During match play, the optimal placement of a ball to beat the opposing goalkeeper is at the top and bottom corners of the goal and the points associated with each scoring zone will reflect this (Fig. 2). Furthermore, a coach would normally encourage the players to shoot across the goalkeeper towards the open space of the goal [12]. To replicate this within the LSST, the players will be told that they can only score points if the ball strikes the open side of the goal, i.e., the half not covered by the mannequin goalkeeper.

Both left and right feet will be used during the LSST. The trial orders will be devised so that players have five shots for each foot per trial. The final score will be the mean of the total cumulative points accrued from all the shots on target. Those shots that were attempted from outside the shooting zone, took more than 8.5 seconds to complete, and/or were struck at less than 64 km · h^-1^, will be completely disregarded.

The assessments will have the same order for every participant regardless of the interventional arm allocation and will be conducted as follows: (1) LSPT numbers 1; (2) LSST numbers 1; (3) LIST-P; (4) LSPT numbers 2; and (5) LSST number 2 (Fig. 4).

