**Fig. 5 Fig5:**
[figure not shown]
SPIRIT flow diagram. (A summary of the planned study interventions and assessments)

Stroop testThe Stroop test is a commonly used neuropsychological tool that measures selective attention and mental processing speed among the cognitive functions that could be affected by attentional fatigue [22]. Campbell et al. utilized the Stroop test in a clinical trial that evaluated participants with T1D during physical activity in a sports camp. The investigators found that reading and color recognition ability were susceptible to impairment as a result of hypoglycemia [12].Commercially available Stroop Color and Word Tests (WPS Publish, Alaska, USA) will be used to assess cognitive processing in our participants. Scores will be determined for reading ability, color recognition, and interference; the latter will be used as an index of the subject’s capacity to maintain attention during the interference caused by the color changes in the typed words [23].Stroop testing will take place immediately following each soccer training session and during the morning evaluation at 8:00 a.m. on the next day. Each of these tests will take 2 to 5 min (time limit of 45 s per slide) for the participants to complete. Participants will be asked to complete the test using three slides: (1) read as many colored words as possible in 45 s; (2) name as many colors of a group of “X” letters as possible in 45 seconds; and (3) name the color in which a word is printed (e.g., “blue”, “green”, or “red” ink) and not the word itself, which is a name of a color (e.g., the word “red” printed in blue ink instead of red ink). Naming the color of the word during this “interference” takes longer and is more prone to errors than when the color of the ink matches the word that names the color [16]. Reading, color naming, and interference scores will be converted to *T* scores according to the manual of Golden and Stroop for further analyses.Digit vigilance testThe digit vigilance test (DVT) works as a measure of sustained attention and psychomotor speed. Participants will be asked to cross out a specific target number (6) as quickly as possible, which appears randomly within 59 rows of 35 single digits on two pages. The examiner will observe the subject's performance on the demonstration rows and then on the first five rows of the test to determine whether corrective feedback is required to discourage an inefficient or poorly motivated response style (e.g., going too fast and missing numbers or going too slow and focusing attention on each individual number). Total time and errors of omission will be recorded. For the first (practice) administration, all participants will be asked to complete the standard format (target = 6) [24].Corsi block-tapping taskThe Corsi block-tapping task (CBT) is widely used for the assessment of visual-spatial short-term memory, both in clinical practice and in experimental research settings. Basically, it is a span task and, as such, a visual-spatial analog to the digit span, as an index of verbal short-term memory. The examiner taps a sequence of blocks, which the participant must repeat subsequently in the correct sequential order. By increasing the length of the sequences, the capacity of the visual-spatial short-term memory can be measured [25].The participant will be seated in front of the examiner, who subsequently will tap the cubes starting with a sequence of two blocks. Two trials will be given per block sequence of the same length. If at least one of these is repeated correctly, the next two trials of a sequence of an increased length will be administered. The cubes will be touched with the index finger at a rate of approximately one cube per second (with no pauses between the individual cubes). The participant will have to tap the cube sequences in the same order immediately after the examiner finishes. The sequences will gradually increase in length. The test will be terminated if the participant fails to reproduce two sequences of equal length. Only a completely, correctly repeated sequence will be scored as correct; self-corrections will be permitted.Rapid visual information processing taskThe rapid visual information processing task (RVIP) is a serial detection task used to probe visual sustained attention and working memory processes. The design of the task consists of a stream of single digits (Arabic numerals 1–9) presented at a rate of 100–110 per minute. Participants are required to detect targets comprising a sequence of three consecutive odd or three consecutive even numbers. In a typical paradigm, targets are presented at a rate of four per 30 s. The critical performance variables include the number of correct responses (“hits”), the reaction time for hits, and the number of errors of commission (response in the absence of a target) [26].This RVIP version will be programmed using e-prime (Version 1.1. Psychology Software Tools, Inc., www.pstnet.com). White numbers between 0 and 9 (excluding 1) will appear in the center of a black computer screen. Each number is presented for 600 ms without a time gap between two succeeding numbers. The participant will have to detect three target sequences (“2–4–6”, “3–5–7”, and “4–6–8”) and respond to them (within 1800 ms after the onset of the last number) by pressing the space bar on the keyboard when the last number of a target sequence appears. The three target sequences will be displayed on the screen during the whole session in order to help the participants remember.Each block will be composed of 150 numbers that appear in a pseudo-random and fixed order; four target sequences will be included in 50 numbers. There will be 72 target sequences that appear during the 9-min test session. In order to prevent a sequence effect, six different RVIP versions will be created by varying these six blocks and then balancing them and pseudo-randomly assigning them to the participants. Hits (H), false alarms (FA) and reaction time (RT) will be recorded by the computer. All RTs shorter than or equal to 100 ms will be excluded from further analyses.

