
In a second step, the sensitivity A, measuring a subject's ability to distinguish targets and non-targets:$$ \left(\mathrm{A} = 0.5 + \left[\mathrm{P}\left(\mathrm{H}\right) - \Big(\mathrm{P}\left(\mathrm{FA}\right) + \left(\left(\mathrm{P}\left(\mathrm{H}\right) - \mathrm{P}\left(\mathrm{FA}\right)\right)2\right]/\right[4\mathrm{P}\left(\mathrm{H}\right)\left(1 - \mathrm{P}\left(\mathrm{FA}\right)\right)\right), $$

the response criterion B, reflecting the individual's response tendency:$$ \Big(\mathrm{B} = \left[\mathrm{P}\left(\mathrm{H}\right)\left(1 - \mathrm{P}\left(\mathrm{H}\right)\right) - \mathrm{P}\left(\mathrm{FA}\right)\left(1 - \mathrm{P}\left(\mathrm{FA}\right)\right)\right]/\Big[\mathrm{P}\left(\mathrm{H}\right)\left(1 - \mathrm{P}\left(\mathrm{H}\right)\right) + \mathrm{P}\left(\mathrm{FA}\right)\left(1 - \mathrm{P}\left(\mathrm{FA}\right)\right), $$

and the SD for the mean RT of each individual will be calculated. Sensitivity A, the number of hits, the SD and the mean RT will be evaluated from two perspectives: the level (e.g., the mean value of A over 9 min) and the time course (e.g., the mean value of A for the first 3 min, the second 3 min and the last 3 min). The number of FA and the response criterion B will be only evaluated from the perspective of level. The SD and the mean RT will only be computed for the hits [27].

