### Statistical methods

In order to evaluate glucose control, we will also compare the two groups, using either Student’s paired *t* test or the Wilcoxon-Mann-Whitney test, in terms of CGM parameters that include: 24-h mean glucose levels, SD of 24-h glucose levels, area under the curve for 24-h glucose, mean amplitude of glycemic excursions, number of episodes of hypoglycemia (<60 mg · dL^-1^), time in hypoglycemia (<60 mg · dL^-1^) during a 24-h period, time in hyperglycemia (>180 mg · dL^-1^) during a 24-h period, and range of postprandial glucose increase. The range of glucose increase (from pre-meal to post-prandial peak levels) after breakfast, lunch, and dinner, will also be compared between the interventional groups, using either repeated measures analysis of variance (ANOVA) or the Kruskal-Wallis test, depending on the normality of the data distribution.

We will assess for data from the LIST-P, LSPT, and LSST, and the Stroop, DVT, DBT, and RVIP test scores obtained for each assessment session, for normality of distribution using histogram analysis, the Shapiro-Wilk test and the Kolmogorov-Smirnov test. We will use a logarithmic transformation for the correction of non-normal data and will subsequently test for the differences between groups using Student’s paired *t* test. In order to assess if the order of the intervention modified the performance of individual participants, we will calculate the difference of the scores obtained between the two types of interventions (real intervention minus sham 4-step method) and then we will define an intervention indicator variable that will take the value of 1 if the subject started with the real 4-step method, and 0 if the subject started with the sham 4-step method. We will then fit a linear regression model with the difference calculated as the response variable and the intervention indicator along with other relevant covariates (age, gender, BMI) as the independent variables. Moreover we will test for time effect over the performance of the participants in a time-varying regression model. Additionally, Pearson correlation coefficients will be calculated between each of the scores and the pre-exercise blood glucose level, searching for linear correlation between blood glucose values and the LIST-P, LSPT, LSST, and Stroop test scores.

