In the event that the data do not follow the normal distribution even after the log-transformation, we will conduct non-parametric analyses using the Wilcoxon-Mann-Whitney test and calculate Spearman correlation coefficients for the comparison between the two groups of the performance scores in soccer and cognitive tests, and for the linear correlation analysis, respectively. A *p* value <0.05 will be considered significant for the comparison of the scores.

Additionally, we will conduct exploratory analyses by modeling the performance scores in soccer evaluations adjusted by age, years since T1D diagnosis, HbA1c level, weekly physical activity hours and Stroop test scores using linear multiple regression. A *p* value <0.10 will be considered significant to introduce a variable into the multivariate regression model. The number of hypoglycemic events and the percentage of other adverse effects listed previously will also be compared among groups using Student’s *t* test and the Fisher exact test, respectively. All of the statistical analysis will be done using Stata software (StataCorp LP® 13.1).

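### The blanket log rule cannot be applied to soccer and cognitive scores that can be zero or negative, and normality is checked on session scores instead of paired differences

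*Protocol article*

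**What the plan says.** The Statistical methods section of the protocol article sets one rule for the LIST-P, LSPT, LSST, Stroop, DVT, block-tapping (printed there as DBT) and RVIP scores.

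- **What is checked:** the "test scores obtained for each assessment session, for normality of distribution using histogram analysis, the Shapiro-Wilk test and the Kolmogorov-Smirnov test".
- **What follows if the check fails:** "We will use a logarithmic transformation for the correction of non-normal data". The analysts "will subsequently test for the differences between groups using" Student's paired t test.
- **Fallback:** "In the event that the data do not follow the normal distribution even after the log-transformation, we will conduct non-parametric analyses". The test named there is Wilcoxon-Mann-Whitney.

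The section gives no offset, no exempt outcome and no rule for values of zero or below.

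The outcome descriptions show what the rule has to cover. For the digit vigilance test, "Total time and errors of omission will be recorded". For the shooting test, "The final score will be the mean of the total cumulative points accrued from all the shots on target". For RVIP, hits, false alarms and reaction time are recorded, and "The number of FA and the response criterion B will be only evaluated from the perspective of level". Criterion B is defined there as a signed ratio.

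**The concern.** There are two separate faults in the stated rule.

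First, a logarithm needs a positive number. Omissions, false alarms, hits and LSST points can be zero, and criterion B can be negative. In Stata, the named software, the log of such a value is missing, and a pair with one missing member contributes nothing to a paired test. Whether a participant stays in the comparison would then depend on the outcome itself. On error counts the best results would be lost; on LSST points and hits, the worst.

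Second, the paired t test assumes approximately normal within-participant differences. Checking each session's scores looks at a distribution dominated by how participants differ from one another, which the pairing removes. This affects every listed score, including strictly positive times.

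At stake are the size and power of the soccer and cognitive comparisons. The primary hypoglycemia outcome is not touched.

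**Working it through.** The document states no figure for this rule, so there is none to reproduce.

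**1. Criterion B (no distributional assumption).** Inputs from the RVIP description: 72 targets and six blocks of 150 numbers, so 6 × 150 = 900 numbers. If each target counts once, 900 − 72 = 828 are non-targets. With h = P(H) and f = P(FA), the printed formula is B = [h(1−h) − f(1−f)] / [h(1−h) + f(1−f)].

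- 71 hits, 14 false alarms: h(1−h) = 71/72 × 1/72 = 0.0137; f(1−f) = 14/828 × 814/828 = 0.0166; B = −0.0029/0.0303 ≈ −0.10.
- 72 hits, 5 false alarms: h(1−h) = 0, so B = −1.
- 72 hits, 0 false alarms: B = 0/0.

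So B can have no logarithm at plausible results.

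**2. Which scores are exposed.** Zero is possible for DVT omissions and RVIP false alarms (best result) and for LSST points and RVIP hits (worst result). DVT total time and RVIP reaction time are positive. LSPT time is positive in practice: at most 16 s can be subtracted over 16 passes.

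**3. Pairs lost if undefined logs stay missing.** Input from Sample size: 24 pairs. The error means are assumed, because the document gives none. For Poisson errors with mean m in each session, P(at least one zero in a pair) = 1 − (1 − e^−m)².

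| m | share of pairs lost | of 24 |
|---|---|---|
| 1 | 0.60 | 14.4 |
| 2 | 0.25 | 6.1 |
| 3 | 0.10 | 2.3 |
| 5 | 0.013 | 0.3 |

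With between-participant variation (gamma-Poisson, shape 1.5, true rate ratio 0.60), the losses at control means 1, 2, 3 and 5 are 17.6, 12.3, 9.2 and 5.8 of 24. The ratio estimated from the remaining pairs is 0.80, 0.72, 0.68 and 0.64. At mean 2, lost participants have a true rate of 1.14 and retained ones 2.91.

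**4. The whole planned sequence.** Simulation: 24 pairs, gamma-Poisson counts, shape 1.5, Shapiro-Wilk on each session, undefined logs left missing, and the fallback taken if either session's logged values fail.

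- **Means 4 v 2:** 33% of pairs contain a zero. The log-plus-t branch, if always taken, has 81% power and estimates the true ratio 0.50 as about 0.57. About 80% of trials are diverted to the fallback. Power of the full sequence is about 62%, against about 94% for a signed-rank test on the pairs.
- **Means 6 v 4:** 19% of pairs contain a zero. Where raw scores fail normality, the logged positive values pass in 62% of trials, so the log t test goes ahead. Power of the full sequence is about 45%, against about 78%.

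At 4 v 2, the drop from 94% to 81% comes from the log branch with lost pairs. The further drop from 81% to 62% comes mainly from sending paired data to an unpaired rank test.

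**5. Session scores versus differences.** Assume a skewed participant level and normal within-participant error (for example, exponential with mean 15 and error SD 4, 24 participants). Session scores fail Shapiro-Wilk in 83% of trials and differences in 5%. A second run under the same kind of assumption gave 72% and 5%. A range of about 65–85% against 5% is fair.

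**The case against.** The strongest reply is that the fallback catches most of the problem. At low counts it is reached often (about 80% of trials at 4 v 2), so the 81% figure for the log branch describes a path the plan usually leaves. That stands, and is why the full sequence is reported above. It does not rescue the plan: the fallback as written is the unpaired Wilcoxon-Mann-Whitney test, and the sequence then has lower power than the log branch alone. If both sessions had to fail before switching, only 10–22% of trials at 4 v 2 would be diverted; the text does not say which reading applies.

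A reader might infer that the plan silently deletes the best performers. The document does not support that. It states no exclusion; loss follows only if undefined logs are left missing. An analyst could add an offset, and log(x+1) keeps every pair with 89% power at 4 v 2, but the plan does not provide for it. Nor is the direction uniform: zero is best for omissions and false alarms and worst for LSST points and hits, while criterion B is a response tendency, not a performance score.

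The sizes rest on assumed error rates, and with Poisson errors the loss is about 1% of pairs at mean 5. Needless transformation after a session-level check is inefficient and changes the scale of the result, but does not by itself invalidate the test.

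Finally, the classical signed-rank test discards zero differences: under equal Poisson means, 21% of pairs tie at mean 2 and 31% at mean 1. That objection is right and shapes the fix.

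**Conclusion.** The concern holds as a fault in a stated rule, not as missing detail. The log step cannot be carried out for criterion B over part of its range, or for zero omissions, false alarms, hits or LSST points. The criterion B result needs only the printed formula and the RVIP counts. Normality is checked on the wrong quantity for a paired t test, which in the assumed skewed-participant setting triggers transformation in roughly 65–85% of trials although the differences would fail in about 5%.

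The power figures (about 62% v 94% and 45% v 78%) are illustrations. They assume gamma-Poisson counts of shape 1.5, 24 pairs, undefined logs left missing and a two-sided 5% level, and part of the gap is due to the unpaired fallback. The loss from dropped zeros shrinks as error counts rise. It would go too far to conclude that the trial's main result is biased: only secondary and exploratory soccer and cognitive scores are concerned. The rule should be corrected before analysis.

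**What to change.** Amend the Statistical methods section as follows.

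- Judge normality on the within-participant differences, not on the scores of each session.
- Allow the log only for strictly positive, skewed measures such as completion times and reaction times.
- For DVT omissions, RVIP false alarms and hits, LSST points and criterion B, analyse untransformed within-participant differences with the Wilcoxon signed-rank test in its zero-retaining (Pratt) version. This also replaces the unpaired fallback for these scores.
- State how criterion B is set when it is 0/0 (all hits and no false alarms); otherwise a perfect performer stays missing under any test.

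The cost is a few sentences. No new data, visits or participants are needed.

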### Trial design

This is a randomized, crossover, double-blinded (subject and evaluator), controlled trial. Participants will be randomized to the order of the interventions assigned (real 4-step method versus usual recommendations (sham 4-step method)), leaving a washout period of 3 weeks for repeating assessments after switching groups. We follow the standard protocol items: recommendation for interventional trials (SPIRIT) guidelines to cover all sections involved in this protocol (see Additional file 1).

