### Baseline assessments

Baseline assessments will be carried out by a physician and will take place after consent has been obtained and before randomization. During this visit (visit 1), a physician will complete an evaluation with clinical data about the subject’s physical activity routine, chronic diabetes mellitus control, history of hypoglycemia, and body mass index (BMI) measurement. Additionally, the following laboratory evaluations will be performed: fasting plasma glucose, serum C-peptide level, HbA1c and urinary albumin excretion in a spot urine sample. Following all baseline assessments the subject will be randomized to their respective arm.

One week after randomization, a second visit (visit 2) will take place during which a certified physical education teacher and a soccer trainer will give the participants a theoretical and practical explanation of the training session exercises that will be conducted in the trial. During this visit, the participants will execute a short version of the simulated soccer exercises to become familiar with them. Additionally, participants will receive an educational session with an endocrinologist with all of the indications to complete the blood glucose management through insulin and dietary adjustments.

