### Outcomes

A physician will follow the participants’ blood glucose levels un-blinded, a week before each assessment session. This control will be based on an email report of the daily blood glucose levels 7 days before the training session.

During each of the assessments (visits 3 and 6; see Table 3) a CGM will be installed at 7:00 a.m. and will be maintained until 48 h after the training session ends. During each of these visits the participants will perform the soccer performance evaluation at 5:00 p.m. These training sessions must be separated by 3 weeks, with the idea of reducing a possible “learning effect” associated with repeated workouts. In the 48 h following each training session, participants will be required to measure their blood glucose level eight times (i.e., 2 h after dinner, before going to bed, at 12:00 a.m., at 3:00 a.m., just before breakfast, 2 h after breakfast, just before lunch, 2 h after lunch, and just before dinner). They will also be provided with a form where they will be required to register the appearance and timing of symptoms of hypoglycemia. Blood glucose level will be evaluated using the Accu-Chek® Nano Glucometer (Roche Servicios SA, Costa Rica) 30 min before each assessment session, after each one of the workouts, and before both the basal and 24-h cognitive tests.

**Table 3 Tab3:** Study visits summary table

Assessments and interventions	Pre-screening	Visit 1	Visit 2	Visits 3, 6	Visit 5	Visits 4, 7
Review of eligibility criteria	X					
Demographic data and clinical evaluation		X				
BMI measurement and laboratory evaluation		X				
Theoretical and practical explanation of training exercises			X			
4-Step method and usual care recommendations educational sessions			X		X	
Training sessions with simulated soccer exercises (LIST-P, LSST, LSPT)				X		
Cognitive evaluations				X		X
Efficacy of blinding assessment					X	X
Revision of self-monitoring of blood glucose after exercise session						X
Approximated time	30 min	60 min	90 min	120 min	90 min	60 min

*BMI* body mass index, *LIST-P* Loughborough Intermittent Shuttle Test Prescribed and Self-Paced, *LSST* Loughborough Soccer Shooting Test, *LSPT* Loughborough Soccer Passing Test

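### The paired t test planned for the soccer, cognitive and CGM outcomes has no period term; the sequence regression is planned only as a check and, as coded, gives the period-adjusted effect in no single coefficient

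*Protocol article*

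**What the plan says.** The trial is a two-period crossover (Trial design): "Participants will be randomized to the order of the interventions assigned", with a 3-week washout.

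For the soccer and cognitive scores, Statistical methods says that the team, after log transformation where needed, "will subsequently test for the differences between groups using Student’s paired *t* test". The CGM parameters are compared "using either Student’s paired *t* test or the Wilcoxon-Mann-Whitney test, in terms of CGM parameters". Neither comparison has a period term.

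Two further models follow for the scores. The first is introduced with "In order to assess if the order of the intervention modified the performance of individual participants, we will calculate the difference of the scores". Its response is real minus sham, and its regressors are an indicator (1 if real came first, 0 if sham came first) plus age, gender and BMI; centring is not mentioned. The second is a time-varying regression that tests for a time effect. Neither is named as the source of the treatment estimate.

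Under Outcomes, the sessions are kept 3 weeks apart "with the idea of reducing a possible “learning effect” associated with repeated workouts". Under Baseline assessments, at visit 2, "the participants will execute a short version of the simulated soccer exercises to become familiar with them".

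**The concern.** In a two-period crossover, a gain from the first session to the second lowers the real-minus-sham difference in people who start with real and raises it in people who start with sham. A paired t test pools the two sequences, so it counts this systematic gap as random error. If the sequences finish with unequal numbers, part of the gap also enters the estimate.

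A period shift is plausible here. The protocol raises learning itself, and the visit 2 rehearsal is a shortened version of the soccer exercises only. Table 3 shows no cognitive evaluation before visit 3. With about 24 completers there is little precision to spare, and the hypothesized benefit in soccer and cognitive performance rests on these comparisons.

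**Working it through.** **Inputs from the protocol.** 24 participants needed; 28 recruited for 15% dropout (24 × 1.15 = 27.6, rounded up to 28); alpha 0.05, taken as two-sided because sidedness is not stated. The sample size concerns hypoglycemia frequency. The plan gives no power figure for the scores, so it has no figure of its own to reproduce here.

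**Assumptions.** The protocol gives neither a score SD nor a learning-effect size. I set the within-sequence SD of the real-minus-sham difference D to 1 on the analysis scale, the true effect τ to 0.6, and varied the period shift π (second session minus first) from 0 to 1.

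**1. What D contains.**
- Real first: E(D) = τ − π
- Sham first: E(D) = τ + π

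**2. What the regression as coded returns.** Without covariates:
- intercept = τ + π
- coefficient of the 1/0 indicator = (τ − π) − (τ + π) = −2π
- treatment effect = intercept + half the coefficient

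If real and sham leave carryovers c_R and c_S, the coefficient becomes −2π − (c_R + c_S), so period and carryover cannot be separated in it.

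Numerical check with τ = 0.6 and π = 0.5 in a large simulated sample:

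| Model | Intercept | Indicator coefficient | Intercept + half coefficient |
|---|---|---|---|
| 1/0, no covariates | 1.10 | −1.00 | 0.60 |
| 1/0, uncentred age, gender, BMI | −0.18 | −1.00 | −0.68 |
| +0.5/−0.5, centred covariates | 0.60 | −1.00 | not needed |

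The second row assumes mean age 30 and mean BMI 24, with slopes of 0.02 and 0.03; its values depend on those choices. The general point does not: with uncentred covariates the intercept refers to a person of age zero and BMI zero.

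**3. Precision, 12 per sequence.** The SD used by the paired t test is about √(1 + π² × 24/23):
- π = 0.5: √(1 + 0.25 × 1.043) = 1.12, so the standard error is 12% larger
- π = 1: √(1 + 1.043) = 1.43, so it is 43% larger

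Simulation, 40,000 trials per case:

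| Period shift (SD) | Paired t power | Period-adjusted power | Paired t type I error |
|---|---|---|---|
| 0 | 81% | 80.5% | 5.1% |
| 0.25 | 79% | 80.5% | 4.4% |
| 0.5 | 73% | 80.5% | 3.0% |
| 0.75 | 64% | 80.5% | 1.4% |
| 1.0 | 50% | 80.5% | 0.6% |

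Both estimates average 0.60 in every row.

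**4. Unequal completers.** Mean of D = τ − π(n₁ − n₀)/n, with n₁ starting on real and n₀ on sham. The size of the bias is therefore:
- 13/11: 2/24 = 8% of π
- 14/10: 4/24 = 17% of π

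With 10 real-first and 14 sham-first, the simulated paired estimate is 0.683 at π = 0.5 and 0.766 at π = 1; the adjusted estimate stays at 0.60.

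**5. How likely the imbalance is.** Small blocks should give about 14/14 of 28, and 15% of 28 is about four dropouts. If dropout is unrelated to sequence, C(28,4) = 20,475 sets of four are equally likely:
- 12/12: 91 × 91 / 20,475 = 40%
- 13/11: 2 × 364 × 14 / 20,475 = 50%
- 14/10: 2 × 1,001 / 20,475 = 10%

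**The case against.** The strongest reply is that the plan takes learning seriously. It calls the effect possible, not expected. It spaces the sessions, rehearses the soccer exercises, randomizes the passing and shooting trial orders, mentions a practice administration of the digit vigilance test and balances six versions of the rapid visual information processing task. These steps may keep the shift small, and at 0.25 SD the loss is only 1 to 2 percentage points. That stands. But they reduce the shift without removing what is left from the paired comparison.

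Four stronger readings are tempting, and the document does not support them.

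- *Period is ignored altogether.* It is not: order and time are both tested. But those tests, as described, leave the treatment estimate and its standard error unchanged.
- *The planned regression already reports the adjusted effect.* It holds the information, but the coding and uncentred covariates mean that no single coefficient shows it.
- *The order check will be misread as a fault of the intervention.* The protocol asks whether order modified performance, and a coefficient made of period and carryover can answer that. Misreading is a possibility, not something the text commits to.
- *The paired test would produce false positive claims.* With balanced sequences it errs the other way. At 10/14 its simulated type I error was also no higher than 5.0%, falling to 2.4% at a shift of 1 SD.

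The learning argument is made for the performance and cognitive tests. For CGM parameters only the general reason for a period term applies.

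**Conclusion.** The point holds, as one of efficiency first and bias second. The stated test of the continuous outcomes omits period, and the two models that address order or time are not tied to the treatment estimate.

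Under the assumed 0.6 SD effect and equal sequences, the cost runs from negligible at a 0.25 SD shift to about 7 points of power at 0.5 SD and 30 points at 1 SD. Bias needs unequal completers; the likely case is none or 8% of the shift, and 17% is the extreme in which all four dropouts leave one sequence. The effect size and shifts are my assumptions, so these figures show a range and are not a forecast.

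Only secondary and exploratory outcomes are concerned. The primary outcome, the percentage of participants with hypoglycemia, lies outside this point.

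**What to change.** In Statistical methods, name a period-adjusted analysis as the main one for the continuous secondary and exploratory outcomes. Either:

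- regress the real-minus-sham difference on sequence coded +0.5 (real first) and −0.5 (sham first), centre any covariates, and report the intercept with its confidence interval as the treatment effect; or
- fit a mixed model with arm, period and participant.

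Label the sequence coefficient as the period effect (plus any carryover). Keep the unadjusted paired t test as a sensitivity analysis.

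The sequence term costs one degree of freedom (23 to 22 with 24 completers); each covariate retained costs one more, as it already would in the planned regression. No new data or participants are needed.
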